| ENDPOINTS                             |                           | Safety and Tolerability: 
 
• Occurrence of local and systemic adverse events
 
• Occurrence of clinically significant hematological and biochemical abnormalities
 
 Immunogenicity: 
 
• ELISA for antibody titers against PEV 301 and PEV 302, performed by Pevion Biotech Ltd.
 
• Western Blotting and IFA for antibody titers crossreactive with P. falciparum parasites (blood stages and sporozoites, respectively), performed by STI
 
 Ancillary: 
 
• T-cell proliferation assays, performed at STI
 
• Parasite growth/invasion inhibition assays, performed at STI
 
• IgG isotyping, performed at STI
 
• ELISPOT and clonal T-cell analyses, performed at STI
 
• Influenza ELISA/HIT, performed at Pevion Biotech Ltd.
 
 |
| METHODOLOGY                           |                           |                                                                                                                                                                                                                                                                                                                                                                                                                                                                                                                                                                                                                                                                                                                                                                                                                                                                                                                                |

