| PLACEBO group F                |                                                   | Virosomes alone                                                                                                                                                                                                                                                                                                                                                                                                                                                                                                                                                                                                                                                                                                                                                                                                                                                                                                                                                                                                                                                                                                                                                                                                                                                                                                                                                                                                                                                                                                                                                                                                                                                                                                                           |

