## 1.2 Virosomes

There is mounting evidence that the majority of natural anti-malarial immune responses (and accordingly responses to entire recombinant malaria proteins) are useless or even counterproductive. Therefore our approach is, to focus the immune response to selected protective epitopes of key malaria antigens.

We have developed new approaches and technologies for the design of epitope-focussed vaccines [1-6]. Starting point was to investigate the possibility of associating peptide or protein antigens in a defined fashion using immunopotentiating reconstituted influenza virosomes (IRIV). These are spherical, unilamellar vesicles, prepared by detergent removal from a mixture of natural and synthetic phospholipids and influenza surface glycoproteins. They have been shown to be a highly effective means of enhancing the immune response to a variety of antigens. The haemagglutinin membrane glycoprotein of the influenza virus plays a key role in the activity of IRIV. This major antigen of influenza virus is a fusion-inducing component, which facilitates antigen delivery to immunocompetent cells. In the hepatitis A vaccine Epaxal, the first licensed vaccine in which IRIV are used as a delivery system for a non-influenza antigen, the hepatitis A antigen spontaneously binds to the IRIV. We have developed and evaluated a method to couple antigens to phosphatidylethanolamine and to integrate the phospholipid-antigen conjugates into the virosome membrane during the virosome reconstitution process. In experiments in mice, the presentation of multiple copies of the antigen on the virosome surface induced strong antibody responses.

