## 3 Study Design

This prospective phase I, single centre, randomized, single blind, placebo controlled, dose escalating study will be conducted in 46 healthy adult volunteers. Eligible study participants will be randomized into six groups: PEV 301 10 µg (group A, n = 8) or PEV 302 10 µg (group B, n = 8) or PEV 301 50 µg (group C, n = 8) or PEV 302 50 µg (group D n = 8) or PEV 301 50 µg plus PEV 302 50 µg (group E, n = 8) or virosomes alone (group F, n = 6).

Study participants will be vaccinated three times, i.e. at days 1, 64(+2) and 183(+2) and followed-up 3 times after each vaccination. If any of the study groups does not show any immune response 3 weeks after the 2nd vaccination, no 3rd vaccination will be given to that group, i.e. the study for that group will be terminated 3 weeks after the 2nd vaccination.

Groups C & D (PEV 301 50 µg; PEV 302 50 µg) will be started 5 weeks after the 1st vaccination of groups A, B.

Group E (PEV 301 plus PEV 302) will be started 5 weeks after the 2nd vaccination of groups C and D.

Group F will be distributed and serve as a control in all groups receiving the active product.

The total duration of the study for each participant is 31 weeks, the number of visits is 13.

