## **4 Study Population**

### **4.1 Number of subjects**

A total of 46 healthy adults (if possible 23 females and 23 males) will be enrolled into the study in order to reach a minimum of 34 evaluable subjects.

Only subjects for whom the investigator believes the requirements of the protocol will be complied with (e.g. completion of the diary cards, return for follow-up visits) should be enrolled in the study.

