## 6.3 Treatment allocation and randomization

Randomization will be computer generated. The investigator will receive envelopes with numbers (1 to 46) corresponding to the sequence of assignment to the study. In the envelope the assignment to the study group will be determined.

The 18 volunteers recruited in October will first be stratified into males and females and then randomized in blocks of 9 (1 block = females, 1 block = males) into 3 groups: Group A (n = 8) will be vaccinated with 10 µg PEV 301, Group B (n = 8) will be vaccinated with 10µg PEV 302, and 2 volunteers will receive virosomes alone (Group F). If it is not possible to have an equal sex distribution, the blocks can be filled with participants of either sex.

5 weeks later again 18 volunteers have to be recruited, they first will be stratified into males and females and then randomized into 3 groups: group C (n = 8) will be vaccinated with 50 µg PEV 301, group D (n = 8) with 50 µg PEV 302, and 2 volunteers will receive virosomes alone (Group F).

5 weeks after the 2nd vaccination of groups C and D 10 volunteers will be randomized in blocks of 5 to either group E (n = 8) receiving the combination of 50 µg PEV 301 plus 50 µg PEV 302 or group F (n = 2) receiving virosomes alone.

| Time          | N  | Dose       | PEV 301 | PEV 302 | PEV 301+302 | virosomes |
|---------------|----|------------|---------|---------|-------------|-----------|
| November 2003 | 18 | 10 µg      | 8       | 8       |             | 2         |
| December 2003 | 18 | 50 µg      | 8       | 8       |             | 2         |
| March 2004    | 10 | 50 + 50 µg |         |         | 8           | 2         |

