### 10.4 Statistical hypothesis

PEV 301 and PEV 302 are safe for inoculation into non-immune subjects. No serious adverse events attributable to either vaccine occur in the study population. One or both of the vaccines induce specific immune responses in at least 1/3 of the volunteers.

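### No planned immunogenicity test compares a vaccine group with volunteers unexposed to its antigen; in cohorts 1 and 2 the other-antigen group could serve (groups A to D only)

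*Protocol*

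**What the plan says.** **Control.** Protocol section 3: "Group F will be distributed and serve as a control in all groups receiving the active product". The Synopsis describes that group as "Virosomes alone". Section 3 gives its size as six and section 6.3 places two in each cohort. For cohort 1, section 6.3 reads: "Group B (n = 8) will be vaccinated with 10µg PEV 302, and 2 volunteers will receive virosomes alone (Group F".

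**Endpoint and hypothesis.** The Synopsis lists "ELISA for antibody titers against PEV 301 and PEV 302, performed by Pevion Biotech Ltd", followed by Western blot and IFA against the parasite. Section 10.4 states: "One or both of the vaccines induce specific immune responses in at least 1/3 of the volunteers". It names no comparator.

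**Tests.** Section 10.6 plans (a) descriptive statistics for each measure, time point and group, (b) each volunteer's ratio to the screening value, and (c) Wilcoxon tests between doses and between group E and C or D. Neither F nor the group given the other antigen appears in (c).

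**Construct.** Section 1.3 identifies PEV 301 as an AMA-1 mimotope and PEV 302 as a CSP mimotope. Section 1.2 describes coupling the antigens to phosphatidylethanolamine and a method "to integrate the phospholipid-antigen conjugates into the virosome membrane during the virosome reconstitution process". Section 6.2 lists the same excipients for every product and no active substance for the virosome-only product.

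**The concern.** A claim that a vaccine raises specific antibody needs a reference for what the assay reads in people who did not receive that antigen. The dose comparison cannot supply it, because both dose groups received the antigen. Group E against C or D cannot either. The one group named as control is in none of the listed tests and has only two members per cohort.

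The design already contains a larger reference. Groups B and D never receive PEV 301, and groups A and C never receive PEV 302. Each is randomised alongside its counterpart, given the same virosome and bled at the same visits.

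This reference also answers something that F cannot. F has the carrier but no conjugated mimetic. It controls for the carrier and for drift over time, but it cannot show whether antibody binds the mimotope itself or a feature common to both conjugates. The other-antigen group can.

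**Working it through.** **1. Allocation (sections 3, 4.1, 6.3).** Five groups of 8 plus six in F: 5 × 8 + 6 = 46. By cohort: 18 + 18 + 10 = 46. Both agree with the stated total.

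**2. Concurrent volunteers unexposed to the tested antigen.**

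| Group tested | F in cohort | Other-antigen group | Total |
|---|---|---|---|
| A or B (cohort 1) | 2 | 8 | 10 |
| C or D (cohort 2) | 2 | 8 | 10 |
| E (cohort 3) | 2 | none (E receives both) | 2 |

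**3. Smallest two-sided exact Wilcoxon p, 2/C(8+m, 8), for m controls.**
- m = 2: 2/45 = 0.044, reached only with complete separation.
- m = 8: 2/12,870 = 0.00016.
- m = 10: 2/43,758 = 0.00005.

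Section 5.5 does not replace withdrawals. If one of the two F volunteers in a cohort is lost, the smallest p becomes 2/9 = 0.22.

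**4. Power of the exact Wilcoxon test.** Simulated with 4,000 runs. Two-sided 0.05, normal log titres and a uniform shift are assumptions; the protocol gives none of them.

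| Comparison | 1 SD | 1.5 SD | 2 SD |
|---|---|---|---|
| 8 v 2 | about 17% | 32% | 52% |
| 8 v 6 (all of F, not concurrent) | 35% | 66% | 89% |
| 8 v 10 | about 46% | 80% | 96% |

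The 8 v 8 comparison lies between the last two rows.

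**5. Responder proportions, the scale of section 10.4.** With no responders among m controls, the two-sided 95% Clopper-Pearson upper limit on background is 1 − 0.025^(1/m):
- m = 2: 84%
- m = 8: 37%
- m = 10: 31%

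For Fisher's exact test against no control responders:
- m = 2: 8/8 vaccinees must respond (1/45 = 0.022); 7/8 gives 8/120 = 0.067.
- m = 8: 5/8 is enough (2 × 56/4,368 = 0.026); 4/8 gives 2 × 70/1,820 = 0.077.
- m = 10: 4/8 is enough (70/3,060 = 0.023).

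Beside a benchmark of one third, a background limit of 84% says nothing. Limits of 37% and 31% are close to the benchmark.

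**6. Combining cohorts 1 and 2.** A cohort-stratified (van Elteren) Wilcoxon test at 1 SD has simulated power of about 33% with 2 controls per cohort and about 79% with 10, with type I error near 0.05. This applies the same shift at 10 µg and 50 µg, which need not hold, so it is only illustrative.

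**The case against.** Much can be said for the plan as it stands, and it rules out several stronger readings.

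- **A reader might infer that F is the designated antibody control and that a weak 8 v 2 test is planned.** Section 3 makes F a control in general and does not tie it to the antibody endpoints. Section 10.6(c) plans no test against F. The 8 v 2 figures show what F alone could offer, not the performance of a planned analysis.
- **A reader might infer that response cannot be judged at all.** Section 10.6(b) uses each volunteer's ratio to baseline, and section 4.3 excludes people with past malaria, long-term residence in an endemic area or a visit in the previous 12 months. A within-person rise is real evidence. A concurrent group adds protection against assay drift and background change.
- **A reader might infer that specific and non-specific antibody cannot be separated.** Western blot and IFA test recognition of the parasite itself, and antibody to linker or lipid would not be expected to pass them. The protocol reports no anti-conjugate antibody, so that worry is a possibility and not a documented problem.
- **A reader might infer that the sample size is wrong.** Section 10.5 disclaims power for differences between regimens, and safety is the primary objective.

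Section 10.6(a), read plainly, may also already display each antigen's titres in every group, though it does not say that both ELISAs are run on all sera.

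Pooling carries a tension. If the other-antigen group and F differ because only one has a conjugate, the pooled control is a mixture. The two must therefore be shown apart first. Shared randomisation blocks are stated for cohort 1 only; cohort 2 is randomised together with no block size given.

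What stands is narrower. The protocol lists its tests, none uses an unexposed comparator, and a concurrent randomised one is available for groups A to D.

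**Conclusion.** The point holds for groups A to D as a cheap improvement to the analysis. It does not correct an erroneous figure or resolve a contradiction. The other-antigen group takes the concurrent unexposed volunteers from 2 to 8, or to 10 with F. On the stated assumptions, 8 v 10 has about 46%, 80% and 96% power at 1, 1.5 and 2 SD, against about 17%, 32% and 52% for 8 v 2. The upper limit on background after no control responders falls from 84% to 31%, or to 37% with the other-antigen group alone.

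Two limits remain. Group E receives both antigens and keeps two concurrent controls; using groups A to D as its reference would be non-concurrent. And because section 10.8 allows any group to stop after the second dose, the other-antigen reference may be missing after the third. The comparison is most secure up to the visit three weeks after the second dose.

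**What to change.** In section 10.6, for groups A to D:

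1. Add, for PEV 301 assays, A v B and C v D; for PEV 302 assays, B v A and D v C. Analyse the ratio to baseline already defined in 10.6(b).
2. Show F separately beside the other-antigen group at every time point. If the two look alike, add the combined comparison (8 v 10) as a supplementary analysis.
3. Combine cohorts 1 and 2 with a cohort-stratified (van Elteren) Wilcoxon test, and also report each cohort alone because the doses differ.
4. State that both ELISAs are run on all sera.
5. State that group E has only its two concurrent F volunteers as unexposed reference, and that third-dose comparisons depend on both groups of a pair continuing.

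The cost is wording, plus possibly some ELISAs for the other antigen on sera already drawn. No extra volunteers or blood draws are needed. If the two antigens cross-react or share conjugate antibody, the contrast is conservative; the separate display of F would help show this.

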|                                              | EXCLUSION CRITERIA | 1. Use of any investigational or non-registered drug or vaccine within 30 days preceding the first dose of study vaccine, or planned use during the study period and safety follow-up.
2. Chronic administration (defined as more than 14 days) of immunosuppressants or other immune-modifying drugs                                                                                                                                                                                                                                                                                                                                                                                                                                                                                                                                                                                                                       |

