|                                |                                                   | 
within six months prior to the first vaccine dose. (For corticosteroids, this will mean prednisone, or equivalent, <math>\geq 0.5</math> mg/kg/day. Inhaled and topical steroids are allowed.)
 
 
Any chronic drug therapy to be continued during the study period.
 
Longterm residency in a malaria endemic area in the past
 
Visit to malaria endemic area within 12 months previous to study start
 
Intention to travel to malaria endemic area during the study period
 
History of clinical malaria
 
Any confirmed or suspected acquired immunosuppressive or immunodeficient condition, including human immunodeficiency virus (HIV) infection, or history of congenital or hereditary immunodeficiency.
 
History of allergic disease or reactions likely to be exacerbated by any component of the vaccine.
 
Acute disease at the time of enrolment. {Acute disease is defined as the presence of a moderate or severe illness with or without fever. All vaccines can be administered to persons with a minor illness such as diarrhea, mild upper respiratory infection with or without low-grade febrile illness, i.e., temperature <math><38^{\circ}\text{C}</math> (<math><100.4^{\circ}\text{F}</math>)}
 
Acute or chronic, clinically significant pulmonary, cardiovascular, hepatic or renal functional abnormality, as determined by physical examination or laboratory screening tests.
 
Acute or chronic diabetes
 
History of chronic alcohol consumption and/or intravenous drug abuse.
 
Pregnant or lactating female.
 
Female planning to become pregnant.
 
 |

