## 1.5 Benefits and Risks

Volunteers will not benefit directly from participation in this study. However, it is hoped that the information gained from this study will contribute to the development of a safe and effective malaria vaccine. The general risks to participants in this Phase I study are associated with phlebotomy and with vaccination. The volume of blood drawn over the study should not compromise these otherwise healthy subjects. Potential risks include the following:

**Local reactions:** Mild tenderness, bruising, or fainting may result from venipuncture. An inflammatory reaction as manifested by redness, swelling, and/or tenderness may occur at the site of vaccine injection. All these local reactions have spontaneously resolved within weeks.

**Systemic Reactions:** Systemic reactions to immunization could theoretically occur, and include a flu-like illness with low-grade fever, chills and malaise. However, experience to date with other CSP vaccines suggests that if such reactions occur, they resolve in 12 days without therapy or limitation of daily activity. Serum sickness reactions due to deposition of antigen-antibody complexes, or idiosyncratic immune responses not dependent on immune complexes could theoretically develop resulting in damage to organs, such as the liver or kidney. Such immunemediated reactions have not been reported to date after malaria vaccines. Temporary ascending paralysis, the Guillain-Barré syndrome, may occur with any vaccine, although it is very rare.

**Allergic Reactions and Anaphylaxis:** As with any vaccine, allergic reactions are possible. A variety of synthetic and recombinant malaria peptide vaccines have induced systemic allergic responses, e.g., urticaria and anaphylaxis. The allergic reactions occurred after 2-3 vaccinations administered at intervals of 1 month or more, vaccines were formulated with Alhydrogel or QS-21 adjuvants, and high antigen concentrations (200 µg - 2000 µg) were inoculated with each dose. Reactions were occasionally associated with development of antigen-specific IgE antibody.

**Adventitious Agents:** Each lot of vaccine is tested for sterility and for either endotoxin content or pyrogenicity. The formulated product is released for use in humans when the release criteria are met, which suggests that the product is free of known microbial contamination that could infect humans. Nevertheless, the risk of unknown microbe is always present.

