### **4.3 Exclusion criteria**

The following criteria should be checked at the time of study entry. If any apply at the time of study entry, the subject must not be included in the study:

1. Use of any investigational or non-registered drug or vaccine within 30 days preceding the first dose of study vaccine, or planned use during the study period and safety follow-up.
2. Chronic administration (defined as more than 14 days) of immunosuppressants or other immune-modifying drugs within six months prior to the first vaccine dose. (For corticosteroids, this will mean prednisone, or equivalent,  $\geq 0.5$  mg/kg/day. Inhaled and topical steroids are allowed.)
3. Any chronic drug therapy to be continued during the study period.
4. Longterm residency in a malaria endemic area in the past
5. Visit to malaria endemic area within 12 months previous to study start
6. Intention to travel to malaria endemic area during the study period
7. History of clinical malaria
8. Any confirmed or suspected acquired immunosuppressive or immunodeficient condition, including human immunodeficiency virus (HIV) infection, or history of congenital or hereditary immunodeficiency.
9. History of allergic disease or reactions likely to be exacerbated by any component of the vaccine.
10. Acute disease at the time of enrolment. {Acute disease is defined as the presence of a moderate or severe illness with or without fever. All vaccines can be administered to

persons with a minor illness such as diarrhea, mild upper respiratory infection with or without low-grade febrile illness, i.e., temperature  $<38^{\circ}\text{C}$  ( $<100.4^{\circ}\text{F}$ )

11. Acute or chronic, clinically significant pulmonary, cardiovascular, hepatic or renal functional abnormality, as determined by physical examination or laboratory screening tests.
12. Acute or chronic diabetes
13. History of chronic alcohol consumption and/or intravenous drug abuse.
14. Pregnant or lactating female.
15. Female planning to become pregnant.

If a subject signs the consent form but withdraws his/her consent after the 1st injection, he/she will abandon the study as of the date of withdrawal. The subject will attest the withdrawal on the consent form and the reason shall be noted at the end of the CRF. Data collected until the date of withdrawal will be used for the statistical analysis of safety.

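### Earlier receipt of an experimental malaria vaccine is barred for only 30 days, so the entry criteria do not secure the non-immune volunteers the hypothesis assumes

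*Protocol*

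**What the plan says.** Section 10.4 of the protocol states the population in its hypothesis: "PEV 301 and PEV 302 are safe for inoculation into non-immune subjects". It adds the immunogenicity expectation: "One or both of the vaccines induce specific immune responses in at least 1/3 of the volunteers".

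The exclusions in the synopsis and section 4.3 (numbered as in 4.3) handle earlier exposure as follows.

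- **Natural exposure.** Exclusion 4 is "Longterm residency in a malaria endemic area in the past", and exclusion 7 bars any past clinical malaria. Neither has a time limit. Exclusion 5 is "Visit to malaria endemic area within 12 months previous to study start", and exclusion 6 is "Intention to travel to malaria endemic area during the study period".
- **Vaccine exposure.** Only exclusion 1 applies: "Use of any investigational or non-registered drug or vaccine within 30 days preceding the first dose of study vaccine", together with planned use during the study. It is a general washout that does not mention malaria vaccines.

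Section 4.3 opens by saying "The following criteria should be checked at the time of study entry". Section 1.5 refers to "experience to date with other CSP vaccines". It also reports urticaria and anaphylaxis with earlier synthetic and recombinant malaria peptide vaccines after two to three vaccinations, occasionally with antigen-specific IgE.

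**The concern.** The protocol treats the two routes to prior priming unequally. Clinical malaria and long-term residency exclude a volunteer for life. A malaria vaccine excludes for 30 days, a period suited to washing out a drug but not to immune memory. Section 1.3 says PEV 302 carries a mimotope of CSP, the antigen for which section 1.5 acknowledges earlier human vaccines.

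Three results would be open to a recall response:

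- the proportion of responders set against the one-third in section 10.4;
- the Wilcoxon comparisons between doses and between group E and groups C or D (section 10.6);
- the interim decision (section 3, section 10.8 and the synopsis), which turns on whether a group shows any immune response after two doses. One primed volunteer could supply that response.

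The primary safety objective is touched too, because section 1.5 links allergic reactions to repeated doses of malaria peptide vaccines. Exclusion 9 covers a history of allergic disease or reactions. It does not cover an earlier vaccination that passed without a reaction.

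**Working it through.** **Step 1: would anything else in the protocol catch a past recipient?** Take a volunteer given a CSP candidate two years before entry.

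| Safeguard | Where | Effect |
|---|---|---|
| Investigational-vaccine rule | 4.3, exclusion 1 | Passes: outside 30 days |
| Malaria-exposure rules | 4.3, exclusions 4 to 7 | Pass: no disease, residency or travel |
| Allergy rule | 4.3, exclusion 9 | Passes if there was no relevant allergic history |
| Screening | 5.2.1 | HIV and influenza A titre; no malaria antibody test for eligibility. The clinical history might reveal the vaccination, but no rule acts on it |
| Per-protocol set | 10.9 | Stays in, because every criterion was respected |
| Ratio to baseline | 10.6 b | Adjusts for existing antibody level, not for a stronger rise on re-exposure |
| Wilcoxon tests | 10.6 c | Stated for the immunological measures, not for the ratios |

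No safeguard removes the volunteer or the recall response.

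**Step 2: how much can one volunteer move a result?** Inputs: 8 per active group and five active groups (section 3). PEV 301 is given in A, C and E, and PEV 302 in B, D and E, so each component is given to 3 × 8 = 24; all active groups hold 5 × 8 = 40. With the 6 controls this gives 40 + 6 = 46, the protocol's total.

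Section 10.4 does not say which denominator the one-third refers to, so all three are shown.

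| Denominator | One volunteer | Smallest count reaching 1/3 | One fewer |
|---|---|---|---|
| One group, 8 | 1/8 = 12.5 points | 3/8 = 37.5% | 2/8 = 25.0% |
| One component, 24 | 1/24 = 4.2 points | 8/24 = 33.3% | 7/24 = 29.2% |
| All active, 40 | 1/40 = 2.5 points | 14/40 = 35.0% | 13/40 = 32.5% |

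A single false responder changes the conclusion only if the count is otherwise exactly one short.

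A Wilcoxon comparison of 8 with 8 rests on 8 × 8 = 64 pairs. One volunteer enters 8 of them, so the share of pairs favouring one group can move by at most 8/64 = 12.5 points, however high the titre.

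**Step 3: how likely is it?** The documents give no rate. If a share p of volunteers were primed, the chance of at least one in a group of 8 is 1 − (1 − p)^8. For assumed p of 0, 1%, 5% and 10% this is 0, 7.7%, 33.7% and 57.0%. These shares are assumptions, and nothing in the protocol points to the upper values.

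**Step 4: the travel anchor.** Exclusions 1 and 2 count from the first vaccine dose; exclusion 5 counts from a study start that is not defined. The protocol's own timing is 5 weeks (cohort 1 to cohort 2) + 9 weeks (dose 1 to dose 2) + 5 weeks = 19 weeks from cohort 1's first dose to cohort 3's. The flow chart agrees: week 46/2003 to week 13/2004 is 19 weeks. Screening, week 45/2003 to week 12/2004, is also 19 weeks apart.

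- If study start means the volunteer's own entry, no travel goes unscreened in any cohort.
- If it means the trial's first screening, trips completed in the roughly 19 weeks before cohort 3 screening fall under neither exclusion 5 nor exclusion 6.

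**The case against.** The strongest reply is that the risk is hypothetical. Section 1.5 says only that experience with other CSP vaccines exists; nothing suggests that recipients are in this single centre's recruitment pool. Section 1.1 says earlier candidates had limited success, so a past recipient need not be immune. The allergic reactions in section 1.5 followed other adjuvants and 200 to 2000 µg of antigen, against 10 or 50 µg per component here. Immunogenicity is a secondary objective, and section 10.5 says the study is not powered for differences between regimens. Baseline samples make existing antibody visible, ratios adjust for its level, and rank tests limit the pull of one extreme titre. All of this stands and keeps the point small. None of it supplies the missing exclusion.

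A reader might also infer that exclusion 5 leaves a travel gap that grows from cohort 1 to cohort 3 and so biases the dose and combination comparisons. The documents do not support stating that as fact. Section 4.3 checks criteria at each volunteer's entry, the schedule of assessments counts study days from each volunteer's own first vaccination, section 3 gives the study duration per participant, and section 8.1 uses the start of the study at subject level. The planned study period in the synopsis and the week count in the flow chart run at trial level, so the term is ambiguous, but the per-volunteer reading has the better support and leaves no gap. Nor does the protocol say that a short visit primes anyone: it accepts visits more than 12 months back.

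**Conclusion.** The vaccine point holds. As written, a volunteer who received an experimental malaria vaccine more than 30 days before the first dose is eligible and stays in the per-protocol analysis, which does not fit a hypothesis about non-immune subjects or the lifetime bars on clinical malaria and long-term residency.

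One such volunteer shifts a response rate by 12.5 points in a group of 8 or 4.2 points among the 24 given a component, and could alone meet an interim rule that asks for any response. This assumes that earlier vaccination leaves a memory response that the study vaccine recalls. How often it would happen cannot be derived from the documents and may be never. No sample-size, power or alpha figure is affected. The priority is low, but an analysis plan cannot change who was enrolled, so the protocol is the place to correct it.

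The travel anchor is an undefined term that needs clarifying, not a demonstrated bias.

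**What to change.** 1. In the synopsis and section 4.3, add an exclusion: *previous receipt of any malaria vaccine at any time*. Keep the 30-day rule for other investigational products.
2. As a clarification in both places, anchor exclusion 5 to the 12 months before each volunteer's first dose of study vaccine, as exclusions 1 and 2 already do.

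The cost is two wording changes, one screening question and possibly a very few volunteers. Sample size, visits and analyses stay as they are.
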